### Statistical analysis

Intention-to-treat (ITT) and per protocol analyses (PPA) will be conducted following the CONSORT recommendations and SPIRIT guidelines for reporting the results [48–50]. Differences in demographic and baseline clinical characteristics will be computed using Chi-square tests for categorical variables and analysis of variance (ANOVA) for continuous data. ANOVA will be conducted to explore the effects of the treatments on all primary and secondary outcomes. Analyses of post-treatment flights will be carried out using Chi-square tests to evaluate group differences, including the number of flights taken and number of safety behaviours performed. Moreover, effect sizes and confidence intervals of the mean will be conducted, following the author’s recommendations and recent literature [66, 67]. Assuming that missing data will be missing at random, it will be handled using multiple imputations (MI) [68]. All analyses will be conducted using IBM SPSS statistics for Windows, version 22.

In any case, the state of the art of analytic methodology for RCT will be reviewed before analyzing the data, in order to apply the most appropriate statistical analysis procedure.

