On the other hand, this type of computer-assisted treatment can be delivered through the Internet, which would improve the advantages of this way of applying exposure, reaching more people in need. The Internet has been shown to be an effective tool for treating a broad range of psychological disorders and psychiatric conditions, particularly depression and anxiety disorders [33–35], and it can address common treatment barriers such as limited access to mental health treatments [35]. Specifically, authors have pointed out five main advantages: efficacy, effectiveness, safety, geographical reach, acceptability, and convenience [36]. However, according to Andersson [33], in spite of the fact that specific phobias are common, only two studies with self-help Internet-based programs have been published, one on spider phobia [37] and one on snake phobia [38].

However, despite the proven efficacy of these programs, there are still some questions that remain unclear, such as the impact of clinician guidance. To date, evidence shows that guidance is a beneficial feature that leads to better adherence and better outcomes in programs administered through the Internet [34, 39–41]. Nevertheless, other authors have shown that unguided self-help interventions are useful alternatives with similar outcomes that might work using automated reinforcement [40, 42, 43]. Moreover, the results so far indicate a small but significant effect size of these self-help interventions compared to a control condition [43–47]. Therefore, more research is needed to examine and determine critical key aspects of clinician guidance that promote positive effects [36].

In sum, the Internet is a useful and effective tool for providing psychological treatments, and there is a large body of research about this topic. However, no published study has explored these issues in the research on FP. As far as we know, no controlled FP study has been published to test the efficacy of an Internet-based treatment.

The purpose of the randomized control trial (RCT) described in this study protocol is to investigate the effectiveness of an Internet-based exposure treatment for FP (*NO-FEAR Airlines*) versus a waiting list control group. Secondary objectives are: a) to explore two ways of delivering *NO-FEAR Airlines*, with or without therapist guidance, and b) to study the patients’ acceptance through expectations, preferences, and satisfaction with the online program. This paper presents the study design.

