### Sample size and power calculations

Power calculations and Internet dropout rates (30 %) [51, 52] were taken into consideration to estimate the necessary sample size to detect a large effect size (*d* = 1) with a power of 0.80 and an alpha of 0.05, based on a similar study [32] and recent systematic reviews [36]. The RCT will recruit a minimum of 57 participants, who will be randomly allocated to one of 3 experimental conditions.

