### Intervention

*NO-FEAR Airlines* is a computer-aided exposure treatment program for FP that can be self-administered via the Internet [53]. This program allows people who are afraid of flying to be exposed to images and sounds related to their phobic fears on a standard personal computer from home. *NO-FEAR Airlines* was developed by LabPsiTec (Laboratory of psychology and technology, Universitat Jaume I, and University of Valencia) in collaboration with LabCDS (University of Balearic Islands). It is a new version based on a previous program *Computer Assisted Fear of Flight Treatment* (CAFFT), created by the LabCSD research group [54, 55], and designed to be completely self-applied over the Internet.

*NO-FEAR Airlines* includes both an *assessment protocol* and a *treatment protocol*. The *assessment protocol* provides a short screening with 19 questions about FP, related problems (i.e., claustrophobia, panic disorder, agoraphobia, and acrophobia), and exclusion criteria. After that, the program carries out a pre-treatment evaluation that includes primary and secondary outcome measures. The *treatment protocol* consists of 3 therapeutic components: psychoeducation, exposure, and overlearning. These three key aspects are based on techniques that have been shown to be effective and conform to recommendations from guidelines on good clinical practice published by international psychology associations such as the American Psychological Association (APA) (www.apa.org) and the National Institute for Health and Clinical Excellence (NICE) (www.nice.org.uk).

The *Psychoeducation* component provides information about what the program will contain, as well as specific information related to FP. Specifically, the program teaches: how many people are affected by the problem; what kinds of people are affected; the physiological, cognitive, and behavioral (or avoidance) components of FP; how it begins and is maintained; and how to cope with the problem. This section contains text, vignettes, and illustrations, in order to make the therapeutic content more attractive to the patient.

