#### Primary outcomes

The Fear of Flying Questionnaire-II (*FFQ-II*) [58] is a 30-item self-report instrument that describes situations related to flying: anxiety during flight, anxiety experienced getting on the plane, and anxiety experienced during the observation of neutral or unpleasant flying-related situations. For each item, respondents rated their degree of discomfort associated with the situation on a scale from 1 to 9 (1 = not at all, 9 = very much). Scores ranged from 30 to 270. As reported by Bornas et al. [58], internal consistency was *α* = .97, and retest reliability (15-day retest period) was *r* = .92.

The Fear of Flying scale (*FFS*) [59] is a 21-item self-report measure to assess fear associated with various air travel situations. Fear elicited by each situation was rated on a 5-point scale (0 = *not at all*, 4 = *very much*), with scores ranging from 0 to 84. For the original FFS [59], Cronbach’s alpha was .94, and retest reliability (at three months) was .86.

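### The outcome analysis is named only as ANOVA, with no baseline covariate and no stated comparison with the waiting list; baseline-adjusted, named contrasts would serve the primary question better

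*Protocol article*

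**What the plan says.** The Statistical analysis section gives one method for every outcome: "ANOVA will be conducted to explore the effects of the treatments on all primary and secondary outcomes". It does not state the form of the model, any covariate or any contrast. The only use of baseline data that it names is a comparison of the groups at entry: "Differences in demographic and baseline clinical characteristics will be computed using Chi-square tests for categorical variables", with ANOVA for continuous variables. It promises effect sizes and confidence intervals, the latter described as intervals of the mean, not of the difference between groups. Its closing paragraph says that the choice of method will be reviewed before the data are analysed.

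The Background section states the primary aim as "to investigate the effectiveness of an Internet-based exposure treatment for FP (*NO-FEAR Airlines*) versus a waiting list control group". Guided versus unguided delivery is secondary.

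Baseline scores will exist. Table 1 lists the FFQ-II and the FFS at baseline, post-treatment and follow-up, and the Intervention section says that "the program carries out a pre-treatment evaluation that includes primary and secondary outcome measures". The Primary outcomes section quotes retest reliability of .92 over 15 days for the FFQ-II; for the FFS, "retest reliability (at three months) was .86".

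**The concern.** An analysis sentence should tell the reader which comparison answers the primary question and how the baseline measurement enters it. This one does neither. Read literally as a one-way ANOVA at post-treatment, it leaves out a measurement that is likely to be prognostic. With about 13 analysable participants per arm, the standard error of a chance difference in baseline means between two arms is sqrt(2/13) = 0.39 SD, and an unadjusted analysis carries part of that imbalance into the estimated effect. Read as a group-by-time ANOVA, it does use the baseline, but less efficiently than ANCOVA.

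On either reading, an overall three-group test by itself shows only that some means differ, and not that treatment beats the waiting list. At stake are precision in a small trial and a clear answer to the main question.

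**Working it through.** **Inputs.** From Sample size and power calculations: "detect a large effect size (*d* = 1) with a power of 0.80 and an alpha of 0.05"; "Power calculations and Internet dropout rates (30 %) [51, 52] were taken into consideration to estimate the necessary sample size"; "The RCT will recruit a minimum of 57 participants, who will be randomly allocated to one of 3 experimental conditions". Assumed because not stated: equal allocation, equal SDs across arms and between baseline and post-treatment, and a within-arm baseline-to-post correlation r between 0.3 and 0.7. No credit is given for information recovered by multiple imputation.

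**The plan's own figure.** Two-group normal formula, n per arm = 2(z_alpha + z_power)²/d².
- One-sided 0.05: 2(1.645 + 0.842)² = 12.4, so 13; 13/0.7 = 18.6, so 19; 3 × 19 = 57. This matches the plan exactly.
- Two-sided 0.05: 2(1.960 + 0.842)² = 15.7, so 16; 16/0.7 = 22.9, so 23; 3 × 23 = 69. This does not match.

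The plan does not state sidedness. The expected number of completers is 19 × 0.7 = 13.3 per arm; 13 is used below.

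**Power for one active arm against waiting list**, two-sided 0.05, 13 per arm. The effective standardised effect is:
- one-way ANOVA: d
- change score (equivalent to group-by-time with two occasions): d/sqrt(2(1 − r))
- ANCOVA: d/sqrt(1 − r²)

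Each is divided by sqrt(2/13) to give the noncentrality of the t-test.

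| r | One-way ANOVA | Change score | ANCOVA |
|---|---|---|---|
| 0.3 | 0.69 | 0.54 | 0.74 |
| 0.5 | 0.69 | 0.69 | 0.82 |
| 0.7 | 0.69 | 0.88 | 0.93 |

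The first two power columns use the 24 degrees of freedom of a two-group test; ANCOVA uses the 3 × 13 − 4 = 35 of the three-arm model. Giving the first two the three-arm error term (36 degrees of freedom) raises them only to 0.70 and to 0.55, 0.70 and 0.89, so the ordering does not depend on this.

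**Where ANCOVA reaches 0.80.** Solving for r gives about 0.47 for a single contrast. If alpha is split to 0.025 over the two active-versus-waiting-list contrasts, power is 0.63, 0.72, 0.80 and 0.88 at r = 0.3, 0.5, 0.6 and 0.7, so r of about 0.6 is needed.

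**ANCOVA against change score.** The variance ratio is (1 − r²)/(2(1 − r)) = (1 + r)/2: 0.65, 0.75 and 0.85 at r = 0.3, 0.5 and 0.7. It never exceeds 1.

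**Pooling the two active arms.** Unadjusted, two-sided 0.05, 13.3 per arm:

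| Means (waiting list, active, active) | Pooled contrast | Three-group F |
|---|---|---|
| 0, 1, 1 | 0.83 | 0.73 |
| 0, 0.5, 1 | 0.585 | 0.594 |
| 0, 0.3, 1 | 0.47 | 0.62 |

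Pooling gains when the arms have similar effects; the gain vanishes and then reverses as they diverge.

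**The case against.** The strongest reply is that the sentence on ANOVA does not say one-way, unadjusted or omnibus-only. Outcomes are taken at four times, so a repeated-measures model that already uses the baseline is plausible. Covariates and contrasts are details that a condensed article may leave to a fuller plan, and the section keeps the method open. This stands in part. A reader might infer that the plan ignores the baseline and relies on an omnibus F; the text does not establish either. But the group-by-time reading is covered above and ANCOVA improves on it too. Nor could a group-by-time test running into follow-up answer the primary question, because the Study design section moves waiting-list participants to treatment after six weeks.

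A reader might also infer that the trial is short of power and that adjustment restores it without conditions. The documents do not support that. The 57 reproduces exactly at one-sided 0.05, so a shortfall exists only if the test is two-sided. Recovery depends on r, and at r = 0.3 ANCOVA on one contrast stays at 0.74. The quoted reliabilities of .92 and .86 are retest figures, not within-arm correlations across a treatment period, so they do not fix r. If r were that high, the variance ratio against a change score would be (1 + 0.92)/2 = 0.96 or (1 + 0.86)/2 = 0.93, a small gain.

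Finally, a reader might conclude that the pooled contrast should be primary because it has more power. That holds only when the two active arms have similar effects. The Background cites evidence that guidance improves outcomes, and the Discussion makes efficacy of the fully self-applied format an aim in itself. Pooling is therefore a design choice.

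**Conclusion.** The point holds in a limited form. The article's analysis sentence names neither a baseline adjustment nor the comparison that answers its primary question, and ANCOVA with named contrasts is a better choice under either reading of ANOVA. At 13 completers per arm, d = 1 and two-sided 0.05, the gain in power on one active-versus-waiting-list contrast is 0.05, 0.13 and 0.24 over one-way ANOVA at r = 0.3, 0.5 and 0.7 (0.74, 0.82 and 0.93 against 0.69). Over a change-score analysis it is 0.20, 0.13 and 0.05 (against 0.54, 0.69 and 0.88).

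These figures rest on equal allocation, equal SDs, 30% dropout with no credit for imputation, and an assumed r. They do not show that the planned analysis is invalid or that 57 is wrong on its own terms. The baseline significance tests are a reporting matter, since nothing in the plan is shown to depend on their result. When baseline scores are collected relative to allocation is a separate procedural question.

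**What to change.** Replace the ANOVA sentence with text to this effect: each outcome at post-treatment, assessed before waiting-list participants cross to treatment, is analysed by ANCOVA or an equivalent mixed model with arm and the outcome's own baseline score; the primary comparisons are the active-versus-waiting-list contrasts; guided versus unguided is secondary; between-group differences are reported with 95% confidence intervals.

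State whether the two active arms are compared with the waiting list separately or pooled, and give the alpha for each contrast. If pooled, say that this presumes similar effects in the two arms. State the sidedness of the 0.05 in the sample size section, and show power over a range of r. Settle this before outcome data are seen, so that the planned review of methods does not leave the primary comparison open.

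The cost is a change of wording and one degree of freedom. No new data are needed, because the baseline scores are already scheduled.

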#### Other measures recorded by the system

##### Measures related to FP

*NO-FEAR Airlines* provides a short assessment of fear and avoidance of flying and checks the following issues: the duration of the problem, how many times the patient has taken a flight, whether safety behaviors were used (e.g., alcohol intake, distraction), and whether the participant has had any negative experiences with flying.

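### Chi-square tests are named for the number of post-treatment flights and of safety behaviours, which are per-participant counts; the test fits only a flew yes/no outcome, which the sentence does not state

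*Protocol article*

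**What the plan says.** The Statistical analysis section of the protocol article gives post-treatment flights a sentence of their own. Their analysis "will be carried out using Chi-square tests to evaluate group differences, including the number of flights taken". The full list of variables under that test is the "number of flights taken and number of safety behaviours performed".

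Under Measures related to FP, the program is said to record "how many times the patient has taken a flight", so the flight variable is collected as a count. Table 1 lists flights taken at baseline, post-treatment and follow-up.

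For baseline comparisons the same paragraph matches test to data type: "Chi-square tests for categorical variables and analysis of variance (ANOVA) for continuous data". Primary and secondary outcomes are assigned to ANOVA. The section closes by saying that the state of the art in trial analysis "will be reviewed before analyzing the data, in order to apply the most appropriate statistical analysis procedure".

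**The concern.** A Chi-square test compares frequencies across unordered categories. A number of flights or of safety behaviours is an ordered count with one value per person. Taken literally, the sentence can be applied to counts in two ways:

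- **Arm by 0, 1, 2, 3... flights.** The difference between 0 and 5 flights then counts no more than that between 4 and 5. Each extra flight value adds cells, most of them nearly empty.
- **Total flights per arm.** Each flight then counts as an independent observation, although flights are grouped within people. A few frequent flyers can produce a significant result.

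The first way tends to miss a real difference. The second can declare one that is not there. The abstract announces the analysis of post-treatment flights separately, and the primary outcomes are self-report questionnaires, so readers are likely to give this comparison weight.

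**Working it through.** **Inputs from the protocol article.** At least 57 participants in three conditions; with equal allocation (an assumption) that is 57/3 = 19 per arm. With the stated 30% dropout, 19 × 0.70 = 13.3, about 13 per arm. The sample-size section is set "to detect a large effect size (*d* = 1) with a power of 0.80 and an alpha of 0.05", a standardised mean difference. The article gives no power figure, expected mean or distribution for flights, so there is no figure to reproduce.

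**Assumptions.** Flights per participant are Poisson, or negative binomial with dispersion k = 2, 1 or 0.5 (variance = mean × (1 + mean/k), so smaller k means more clustering). Each scenario was simulated a few thousand times. At 2,500 runs the Monte Carlo standard error is at most √(0.5 × 0.5/2,500) = 0.01, so differences of one or two points are noise.

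**1. Arm-by-count table, 19 per arm, means 0.3/1.0/1.5**

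| Counts | Chi-square power | Kruskal-Wallis power | Relative loss |
|---|---|---|---|
| Poisson | 74% | 95% | (95 − 74)/95 = 22% |
| k = 2 | 42% | 84% | (84 − 42)/84 = 50% |
| k = 1 | 22% | 70% | (70 − 22)/70 = 69% |
| k = 0.5 | 9% | 48% | (48 − 9)/48 = 81% |

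A second set of means, 0.5/1.5/1.5, shows the same pattern and adds the yes/no analysis:

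| Counts | Table Chi-square | Flew yes/no Chi-square | Kruskal-Wallis |
|---|---|---|---|
| Poisson | 0.55 | 0.74 | 0.89 |
| k = 2 | 0.26 | 0.52 | 0.68 |
| k = 1 | 0.13 | 0.38 | 0.50 |

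Here 64-80% of table cells have an expected count below 5 at 19 per arm, and 84-87% at 13 per arm. At 13 per arm, power for the table against Kruskal-Wallis is 0.35 v 0.70, 0.16 v 0.49 and 0.09 v 0.36.

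**2. Total flights per arm, no true difference.** With mean μ, each arm total has variance φ times its mean, where φ = 1 + μ/k. The Chi-square statistic on 2 degrees of freedom is therefore inflated by about φ, and the false-positive rate is roughly exp(−5.99/(2φ)) = 0.05^(1/φ).

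| μ | k = 2 | k = 1 | k = 0.5 |
|---|---|---|---|
| 0.4 | φ = 1.2: 8.2% | φ = 1.4: 11.8% | φ = 1.8: 18.9% |
| 1 | φ = 1.5: 13.6% | φ = 2: 22.4% | φ = 3: 36.8% |

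Simulation at 19 per arm gives about 8-18% at mean 0.4 and 14-34% at mean 1 across k = 2 to 0.5, in line with the approximation. Under Poisson counts φ = 1 and the rate stays at 4-5%.

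**3. Flew yes/no.** Chi-square on a 3 × 2 table has a false-positive rate of about 4-7%. Against Kruskal-Wallis it loses 6-23% of the power on means 0.3/1.0/1.5, and about a quarter at most on 0.5/1.5/1.5.

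**4. Kruskal-Wallis on per-participant counts.** The false-positive rate is about 4-6% in every null scenario.

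**The case against.** The strongest reply is that a third reading is natural: how many participants in each group flew. The Intervention section encourages patients to take a real flight and treats it as a single test flight. Measures related to FP asks whether safety behaviours were used, which is also yes/no. The same analysis paragraph ties Chi-square to categorical variables. On that reading the test is valid and the power loss is modest. This stands as a possible intention, but the sentence names the number of flights and the number of safety behaviours, and it gives no dichotomy.

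The size of the problem also depends on overdispersion that the article does not quantify. The waiting-list group moves to treatment after 6 weeks, so a randomised three-arm comparison covers a short window in which mean flights may be low. That stands too. At low means the inflation on totals is smaller, and under Poisson counts it disappears. The table still loses power under Poisson counts.

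The closing promise to review methods leaves room for a better test. It names none, and participants and researchers are not blind to condition, so it does not repair the test that is stated.

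A reader might also infer that flights are the trial's only behavioural outcome. The article does not say so, and safety behaviours stand in the same sentence. Nor are flights a primary outcome: those are the FFQ-II and the FFS, and flights appear among the other measures recorded by the system.

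**Conclusion.** The named test does not suit the two variables it is assigned to, and it departs from the article's own rule for matching tests to data types at baseline. At about 19 per arm and means 0.3/1.0/1.5, the arm-by-count Chi-square gives up between 22% (Poisson) and 81% (k = 0.5) of the power of a rank test. The test on arm totals exceeds 5% whenever counts are overdispersed, reaching 8-18% at mean 0.4 and 14-34% at mean 1 for k = 2 to 0.5.

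It would go too far to say that the plan must either lose most of its power or produce false positives well above 5%. The flew yes/no analysis avoids both, Poisson counts keep the totals test at 5%, and all sizes rest on assumed means and dispersion. The quantified results are for flights; for safety behaviours the argument is the same in kind, but no size was computed. The correction should be made, but it does not touch the primary analysis.

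**What to change.** Replace the sentence on post-treatment flights in the Statistical analysis section so that it provides for:

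- the proportion of participants with at least one flight in the stated period, compared by Chi-square or Fisher's exact test, with a risk difference and 95% CI;
- the number of flights and the number of safety behaviours per participant, with the participant as the unit, compared by Kruskal-Wallis, or by a negative-binomial model with observation time as offset and a rate ratio with 95% CI. The baseline count can enter as a covariate in that model only, since a plain rank test takes none;
- no Chi-square test on the counts or on total flights per arm.

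The choice between the rank test and the model should be written down before outcome data are seen.

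Cost: one sentence. Flights are already collected at baseline, post-treatment and follow-up (Table 1), so no new data are needed; the offset uses the interval between assessments.

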### Recruitment, randomization and blinding

The study will be advertised online via professional websites (i.e., LinkedIn), non- professional social-networks (i.e., Facebook and twitter), and advertisements in newspapers. Furthermore, posters will be placed in local universities (Universitat Jaume I and Universitat de València) and travel agencies. People who are interested will be directed to the research website (www.fobiavolar.es), where they will find further information about the study and what participation entails, as well as an informed consent form. Individuals can request participation through the website and by signing the informed consent form. After website registration, the clinical team will contact participants by telephone to screen for the inclusion and exclusion criteria and explain the research terms (i.e., study design, treatment length, or treatment rationale). Participants who meet the criteria will be administered a diagnostic telephone interview at the time of the screening, or another time will be arranged. Then, participants will be randomly assigned to one of the three experimental groups. The allocation schedule will be generated through a computer randomization program (Epidat 4.0) by an independent researcher who will be unaware of the characteristics of the study. The allocation schedule will be communicated to the study researchers via phone call. Patients will agree to participate before the random allocation and without knowing to which treatment they will be assigned. However, for practical reasons, participants and researchers will not be blind to the treatment conditions. Participants will be free at any time to withdraw from the treatment or the study without giving any explanation.

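### An open clause lets the stated ANOVA be replaced at any time before analysis, with no cut-off tied to access to outcome data, so the 5% level is unprotected

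*Protocol article*

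**What the plan says.** The Statistical analysis section of the protocol article first commits to a method: "ANOVA will be conducted to explore the effects of the treatments on all primary and secondary outcomes". Missing data are to be handled by multiple imputation, and both intention-to-treat and per-protocol analyses are planned.

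A separate closing sentence then qualifies this: "In any case, the state of the art of analytic methodology for RCT will be reviewed before analyzing the data", and the stated purpose is "in order to apply the most appropriate statistical analysis procedure".

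Three other places bear on the point:

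- Recruitment, randomization and blinding: "participants and researchers will not be blind to the treatment conditions".
- Ethics: important changes to the protocol are to be communicated to several parties, trial registries among them. No time is set for doing so.
- Sample size and power calculations: the trial is planned "with a power of 0.80 and an alpha of 0.05".

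**The concern.** A protocol can leave details of a model to a later analysis plan. This sentence does something different. It is a written rule that makes the named method replaceable, whatever the circumstances, up to the moment of analysis. It names no trigger such as failed assumptions and no criterion for what counts as most appropriate. It does not promise that the ANOVA will still be reported.

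The weak point is the timing. A review before analysis need not come before the outcomes exist or are visible. Table 1 has FFS, a primary outcome, collected by phone call, FFQ-II collected by the program, and the severity scale rated by the clinician. These data accumulate during the trial among researchers who know the allocation.

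If the method is settled once those data can be seen, a reader cannot tell whether it was chosen on its merits or for its result. The nominal 5% then holds only if the researchers did not look, and the plan gives no means of checking that.

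**Working it through.** **The plan's own figure.** The simulation needs a size per arm, so the planned total was reproduced first. Inputs from Sample size and power calculations: d = 1, power 0.80, alpha 0.05 (sidedness not stated), dropout 30%, three arms, minimum total 57.

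- Formula: n per arm = 2(z_alpha + z_power)² / d².
- One-sided: 2(1.645 + 0.842)² = 12.4, so 13. Then 13 / 0.7 = 18.6, so 19, and 3 × 19 = 57. This matches.
- Two-sided: 2(1.960 + 0.842)² = 15.7, so 16. Then 16 / 0.7 = 22.9, so 23, and 3 × 23 = 69. This does not match.

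The present point does not depend on which was used. It takes only 57 / 3 = 19 per arm, assuming equal allocation.

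**What the texts fix, side by side.**

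| Question | Answer in the article |
|---|---|
| Default method | ANOVA |
| Can it be replaced? | Yes, after a review of methodology |
| Latest time for replacement | Before analysis |
| Cut-off relative to access to outcome data | None stated |
| Researchers blind to condition? | No |
| Deadline for communicating or registering a change | None stated |

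**Size of the worst case.** Trials were simulated with no treatment effect: 19 per arm, complete data, normal scores, 6,000 trials per setting. Assumptions that are not in the document: baseline–post correlation r of 0.3, 0.5 or 0.7, and a correlation of 0.7 between the two primary outcomes.

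Each test is the three-group F test, F = [(RSS₀ − RSS₁) / 2] / (RSS₁ / df). Here df = 57 − 3 = 54 for post-score and change-score ANOVA, and 57 − 4 = 53 for ANCOVA. The worst case counts a trial as positive if the smallest of the candidate p-values is below 0.05.

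| r | Post-score ANOVA | Change-score ANOVA | ANCOVA | Best of three, one outcome | Best of three, either primary outcome |
|---|---|---|---|---|---|
| 0.3 | 5.5% | 4.7% | 5.1% | 9.4% | 14.9% |
| 0.5 | 5.3% | 5.0% | 5.1% | 10.0% | 15.9% |
| 0.7 | 5.0% | 5.3% | 5.0% | 10.7% | 17.5% |

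The Monte Carlo standard error is √(0.05 × 0.95 / 6,000) = 0.3 percentage points near 5%, and √(0.17 × 0.83 / 6,000) = 0.5 points near 17%. Repeat runs of the either-outcome worst case gave 15.7% to 17.1%.

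**The right comparator for two outcomes.** With ANCOVA fixed and no choice of method at all, the chance of a false positive on either primary outcome was 8.1% to 9.3% under the same model. At r = 0.7, one run gave 8.5% for the fixed method, against 16.9% for the best of three. The factor due to choice of method is therefore:

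- one outcome: about 10% / 5% = 2;
- either outcome: 16.9% / 8.5% = 2.0.

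**The case against.** The strongest reply is that the clause describes good practice. What it reviews is the methods literature, not the trial's results, and it places the review before analysis. On that reading ANOVA stays the default and would change only to follow better guidance. A single method chosen that way keeps about 5%, as the table shows. The best-of-three figures require running all three tests and reporting the most favourable one, which a method fixed before analysis would not involve. This stands as a limit on size: the figures illustrate a worst case and do not predict what will happen.

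A reader might infer that the clause cancels the ANOVA, that researchers will choose after seeing results, or that the reported p-values cannot be interpreted. The text supports none of these. It permits a late choice but does not state a data-driven one. Nor may the whole step from 5% to 17% be charged to the clause, because part of it comes from having two primary outcomes.

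The blinding statement concerns treatment conditions. It does not say who analyses the data or whether that person sees group results as they accumulate. It shows that no stated barrier exists, not that access will occur.

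Finally, a separate analysis plan may fix the method, and the Ethics section does promise to communicate important modifications. Both help, but neither closes the gap. The clause refers to no such plan or lock date, so a plan written just before analysis would comply with it. The Ethics promise has no deadline, and a change the protocol already allows might not count as a modification.

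**Conclusion.** The point holds as a badly fixed rule about timing. The article names a method and then lets it be replaced until analysis begins, without tying that freedom to a moment before outcome data can be seen. The 5% level is left unprotected; it is not shown to be exceeded.

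In the worst case, free choice among three individually valid tests roughly doubles the false-positive rate: from about 5% to about 10% on one outcome, and from about 8–9% to about 15–17% on either primary outcome. These sizes rest on the assumed correlations, normal complete data, equal arms of 19 and a search for the most favourable result. The 8–9% is a multiplicity question in its own right, and settling the method does not resolve it.

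**What to change.** Replace the closing sentence of the Statistical analysis section with wording such as:

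> The primary analysis is a baseline-adjusted comparison (ANCOVA) of FFQ-II and of FFS at post-treatment. Any change of method will be dated and entered in the trial registry before any post-treatment outcome data are opened; methods adopted later are reported as sensitivity analyses only.

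The cut-off is the essential part. ANCOVA is proposed because it uses baseline scores the trial already collects and leaves one named test where the article now has a replaceable one. The authors can still update the method, provided they do so early and on record.

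The cost is a wording change and a registry update, with no effect on participants, sample size or conduct. The downside is that a method adopted after the cut-off can only be supportive. How the two primary outcomes share the 5% needs its own decision.
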